## Abstract

**Background:**

The high academic demands experienced by students will often have an impact on the quality of their mental and physical health. The most common health problems reported are gastrointestinal disorders. This condition tends to manifest in the emergence of generalized anxiety disorders (GADs) and reduces the quality of life and productivity. The population that experiences this disorder the most is female adolescents, and this condition occurs in both South African and Indonesian populations. The use of drugs, especially benzodiazepines, often causes psychological conditions as side effects. For this reason, it is necessary to have a solution in the form of a targeted and efficient approach to reduce psychological symptoms that arise from functional gastrointestinal disorders (FGIDs) in the form of anxiety.

**Objective:**

The purpose of this study is to produce and implement a counseling intervention model to assist female students with GADs caused by FGID factors using an approach combining cognitive behavioral therapy (CBT), web-based counseling, and local wisdom in Indonesian and South African populations.

**Methods:**

The research subjects will comprise 118 female adolescent students from Indonesia and 118 female adolescent students from South Africa, making a total sample of 236 participants, and the study will use a prospective, parallel randomized controlled trial design. The recruitment process will begin in July 2023, and the trial will begin in August 2023. The posttest assessment data gathering will take place by November 2023. Questionnaires that will be used in this study include the Functional Gastrointestinal Disorder Checklist (FGI-Checklist) to collect data related to FGIDs and the Generalized Anxiety Disorder 7-item (GAD-7) to measure the anxiety conditions experienced by respondents.

**Results:**

By adopting the intention-to-treat principle, there will be significant mean changes in GAD scores and FGID scores after exposure to this combined approach in the Indonesian and South African populations. Implementing this comprehensive intervention will improve the students’ psychological symptoms related to FGIDs and ultimately enhance their overall well-being.

**Conclusions:**

This study will develop and implement a model of counseling intervention for female students with GADs obtained from FGIDs using a combination approach to CBT, web-based counseling, and local wisdom in both the Indonesian and South African populations. The trial findings will contribute to our understanding of the effects of CBT combined with local wisdom and web-based counseling approaches that mental health counselors can use to treat GAD-affected adolescent girls who have FGIDs.

**Trial Registration:**

UMIN Clinical Trial Registry UMIN000051386; https://tinyurl.com/yjwz8kht

**International Registered Report Identifier (IRRID):**

PRR1-10.2196/50316

## Introduction

### Background

Students experience various changes and challenges over the period of their studies. The high academic demands that students must meet and the tendency for weak control over health impact students’ conditions [1,2]. Various mental health disorders also tend to increase during an individual’s time as a student [3-5]. This condition tends to cause health problems and affects students’ quality of life and mental condition. Disorders that appear commonly in students are functional gastrointestinal disorders (FGIDs) [6,7], which are characterized by abdominal pain, dysphagia, dyspepsia, diarrhea, constipation, bloating, and acute gastrointestinal (GI) disturbances [7-9]. Based on data from the Ministry of Health of the Republic of Indonesia in 2020, FGIDs are included in the list of 10 diseases that affect adolescents the most in Indonesia, with a prevalence of up to 40.85% [10]. FGIDs appear in conditions without an organic basis and are more likely to occur due to impaired communication between the brain and the gut. In other words, disturbances in digestive function are reciprocal. Individuals with FGIDs tend to experience anxiety disorders, while individuals with dominant anxiety conditions will experience digestive disorders [8,11-14]. Treating FGIDs based on the latest findings generally still relies on drug therapy, but this therapy tends to produce other side effects subsequently experienced by the patient [15]. In addition, FGID treatment, which essentially does not produce organic conditions, is time-consuming and expensive. In addition, the patient’s anxiety condition often does not subside and worsens [13,16].

When viewed from a demographic perspective, anxiety disorders as a result of FGIDs are often experienced by the female population during their reproductive years [17,18]. It has been found in population-based case-control studies that women with FGIDs experience a more negative impact on their daily functioning than their male counterparts and other women without this condition [12]. In the South African population, 8% of the total population experienced this; in the KwaZulu-Natal province of South Africa, it was found that among 201 rural patients who presented with one type of FGID (functional dyspepsia), most patients (74.13%) [19] reported anxiety disorders. The impact is that if anxiety conditions and FGIDs are not handled properly, this will decrease students’ productivity and quality of life. Generally, this impact will result in a decrease in students’ opportunities for achievement and learning outcomes to the point of being unable to continue their studies [9,13,16,20]. Anxiety resulting from FGIDs also contributes significantly to the decline in quality of life. It impacts both the student’s college life in terms of their learning, social, and personal lives, and the condition of their future career. Various attempts to alleviate this problem have been made but have not yielded significant results. Among others, a pharmacotherapeutic approach relieves anxiety symptoms that arise [15,21]. However, the use of drugs, especially benzodiazepines, often causes side effects on psychological conditions. For this reason, it is necessary to have a solution in the form of a targeted and efficient approach to reduce psychological symptoms that arise from FGIDs in the form of anxiety [22-41]. With a specific target on anxiety sufferers in the female population of student age, it is deemed appropriate to provide a cognitive behavioral therapy (CBT) approach combined with the implementation of web-based counseling and local wisdom. The advantage of this approach is that the assessment process can be carried out in a remote setting using web-based counseling technology developed in the author’s previous research, then combined with an approach that has proven effective in conducting behavioral change therapy and emphasizes the implementation of local wisdom. In addition, the combination of these 3 elements will be able to spur positive changes in the anxiety experienced by female students with FGID conditions.

### Objective

The purpose of this study is to produce and implement a counseling intervention model to assist female students with generalized anxiety disorders (GADs) caused by FGID factors using an approach combining CBT, web-based counseling, and local wisdom in Indonesian and South African populations.

### Hypothesis

Based on the understanding that students face various challenges and changes during their university studies, including the high academic demands and potential impact on their health, particularly in terms of mental health, it is important to address these issues effectively. One common disorder among students is FGIDs, which not only affect their physical well-being but also have an impact on their quality of life and mental state. Additionally, anxiety disorders often coexist with FGIDs, further exacerbating the negative effects on students’ overall well-being. Considering the prevalence of FGIDs and anxiety disorders among female students, it is crucial to develop an intervention model that combines CBT, web-based counseling, and local wisdom. Thus, this study hypothesizes that there will be significant mean changes in GAD scores and FGID scores after exposure to this combined approach in the Indonesian and South African populations. Implementing this comprehensive intervention is expected to improve the students’ psychological symptoms related to FGIDs and ultimately enhance their overall well-being.

## Methods

### Research Design

This study is developmental research involving the systematic and conceptual design of a psychological treatment approach. The development model that will be used as the basis for this research activity is one adapted from the ADDIE (Analysis, Design, Development, Implementation, and Evaluation) model [42,43]. A prospective, parallel randomized controlled trial design involving pre- and posttesting of a treatment group and a control group will be used by the researchers [44]. At the end of a diagnostic interview conducted by the researchers, participants who are considered eligible for the study will be randomly assigned to 1 of 2 groups: the web-based CBT group or the usual care control group.

### Research Subjects

The research subjects will consist of female adolescent students in Indonesia and South Africa (aged 15-17 years); 118 people from each country will be recruited from general practice or family medicine clinics as well as high schools within each study area to arrive at an overall sample of 236 participants for this study. An initial assessment will be conducted on 1000 potential participants (500 adolescent girls per country), who will be screened according to the research criteria so that a representative sample for the intervention may be obtained. The results of a recent study [45] found that 44.1% of participants were able to complete a CBT program using a web-based approach and that the average completion rate for the 12 sessions was 7.8 (65%). Therefore, we will take into account the attrition rate of 55.9% by including 55.9% extra participants in our initial sample for each group produced by the G*power (Heinrich-Heine-Universität Düsseldorf) sampling program [46]. To account for the potential effects of missed sessions in a standard web-based CBT program, as shown by recent research [45], 4.2 sessions (35%) will be added to the 12-session program, which will result in approximately 16 sessions (to be delivered over 4 months). Based on the G*power calculation, the required sample size is 38 participants per group (85% statistical power; medium effect size Cohen *d*=0.5; a priori probability level of 0.5) for a linear mixed model (LMM) analysis. Given the presumed attrition rate, we will recruit 59 participants per group in each country.

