### Randomization and Masking

This study will use a computer-generated random list obtained from Random Allocation Software [47] to randomize groups using a simple randomization technique by 2 biostatisticians (1 for each country) who are not part of the research team to ensure assignment concealment. Each country’s research team is expected to have 59 research subjects in the treatment group and 59 research subjects in the control group, totaling 118 adolescent girl participants from each country. The group randomization process will be concealed from the study subjects. Thereafter, the researchers will notify subjects of their group membership through invitations to participate in the treatment intervention or usual care sessions.

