### Data Analyses

The analyses of the data in this study will include descriptive analysis, analysis of the coefficient of agreement between program raters (interrater reliability), and internal consistency analysis using Cronbach α and partial η^2^ (effect size statistics). A sensitivity analysis will also be carried out to avert potential data dredging. The Mauchly sphericity test and Levene equality of variance test will be carried out to ensure that the assumptions of the chosen statistical test are met. LMM will be used to analyze the primary outcome measures statistically based on the principle of intention-to-treat to determine whether considerable changes have occurred over time [51]. By using LMM, participants with incomplete data will be included in the analyses so that treatment effects can be assessed over time (group time interaction) [51]. Using LMM, the treatment group, time, and interactions between the treatment group and time will be considered fixed factors; the covariance structure will be constructed in an unstructured manner. We will ascertain posttest outcomes in terms of mean changes in GAD-7 and FGI-Checklist scores from baseline to 4 months following the pretest. Complier-adjusted causal effect (CACE) analysis will be conducted based on the causal framework and estimation methods to account for variations in treatment effect due to variations in treatment adherence between the groups [51,52]. We will calculate CACE as the difference between the mean GAD-7 and FGI-Checklist scores of compliers in the treatment group as well as the control group. To be considered a complier, a participant must have attended 80% or more of the program sessions, which is a frequently used threshold [51,53]. A bootstrapping technique will be used to determine standard errors. Statistical analyses will be completed using R (R Core Team) to analyze the CACE data and SPSS (version 29; IBM Corp) for the rest of the analyses. *P* values of .05 or less will be considered statistically significant.

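### The 59 per group covers a loss of at most 35.6%, not the 55.9% attrition it is said to allow for

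*Protocol article*

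**What the plan says.** All the terms are in the protocol article, Methods, Research Subjects. A cited study "found that 44.1% of participants were able to complete a CBT program using a web-based approach", and the complement, 55.9%, becomes the attrition rate. The requirement from G*power is given as "the required sample size is 38 participants per group", for 85% power and a Cohen d of 0.5. The allowance is put in words: "we will take into account the attrition rate of 55.9% by including 55.9% extra participants in our initial sample for each group". The result follows: "Given the presumed attrition rate, we will recruit 59 participants per group in each country". Randomization and Masking repeats the target for each country as "59 research subjects in the treatment group and 59 research subjects in the control group", 118 in all, and the two countries together make 236. No other section revises the allowance.

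On the analysis, Data Analyses plans an intention-to-treat linear mixed model and says "By using LMM, participants with incomplete data will be included in the analyses". Its fixed effects are group, time and their interaction. No country term is listed.

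**The concern.** An allowance for attrition should return the required number after the expected loss. If a fraction a is lost, the number randomised must be n/(1 − a). The article uses n × (1 + a). The two nearly agree when a is small, but at 55.9% they are far apart. The 59 per group is presented as protecting the calculated size against the very loss the article predicts, and on the article's own figures it does not. This is the only justification given for the trial's size, so a reader would believe that 85% power survives 55.9% attrition when that has not been shown.

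**Working it through.** **Inputs.** Research Subjects: 38 required per group, attrition 55.9% (so 44.1% retained), 59 recruited per group per country, d = 0.5, power 85%. Data Analyses: significance level .05. Two-sided testing is my assumption, because the article does not state it.

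**Reproducing the plan's figure.** 38 × (1 + 0.559) = 59.24, rounded to 59. This matches both the printed number and the method described in words.

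**The allowance that would keep 38.** 38/(1 − 0.559) = 38/0.441 = 86.2, rounded up to 87.

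**What 59 covers.** 1 − 38/59 = 0.356, so a loss of up to 35.6%.

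**What remains at a 55.9% loss of posttests.**
- Per group per country: 59 × 0.441 = 26.0, which is 12 below 38 (12/38 = 32% short).
- Per group with the countries pooled: 118 × 0.441 = 52.0.

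**Where 38 comes from.** The article does not name the G*power test.
- A one-sample or paired t-test with d = 0.5, two-sided 0.05 and 85% power gives 37.9, so 38.
- A group-by-time interaction with f = 0.25, two groups, two times and a correlation of 0.5 gives 85.1% power at a total N of 38. The article, however, says per group.
- A two-sample t-test with d = 0.5 and two-sided 0.05 needs 72.8, so 73 per group, and does not give 38.

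**Power at d = 0.5, two-sided 0.05 (t-tests).**

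| n per group | Paired or one-sample | Two-sample |
|---|---|---|
| 38 (required) | 85.1% | 57.6% |
| 26 (per country, 55.9% lost) | 68.8% | 42.4% |
| 52 (pooled, 55.9% lost) | 94.3% | 71.4% |
| 59 (per country, no loss) | 96.5% | 76.8% |

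**Separating the two sources of shortfall.** On the paired basis, going from 38 to 26 costs 85.1 − 68.8 = 16.3 points, all from the attrition step. On the two-sample basis the gap from 85% to 42.4% is 42.6 points. Of these, 85 − 57.6 = 27.4 are already lost at the full 38, and 57.6 − 42.4 = 15.2 come from the attrition step.

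**The case against.** Four points can be made for the plan.

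*Non-completion is not outcome loss.* The 44.1% is a programme completion rate from another study, not a questionnaire return rate. Under the planned intention-to-treat mixed model, a participant who stops attending but answers the posttest counts in full. If all did so, 59 per group would be analysed. The rate also comes from a web-based CBT programme, yet it is applied equally to the usual care group. This stands as a limit on the consequence: 26 is what remains if every non-completer gives no posttest, and is not a forecast. It does not rescue the allowance. The article itself calls 55.9% attrition and sizes both groups for it. The mixed model recovers little about change at 4 months from a participant with a baseline score only. If posttests are expected from non-completers, then 55.9% was the wrong input.

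*The countries may be pooled.* With no country term in the model, 52 per group would remain, which is above 38. This stands in part. Research Subjects applies 59 per group in each country, which favours the per-country reading, but the article does not settle it.

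*The basis of 38 is itself unclear.* Research Subjects prints an "a priori probability level of 0.5) for a linear mixed model (LMM) analysis", whereas Data Analyses says that "values of .05 or less will be considered statistically significant". If 38 were really a total N for the interaction test, 26 per group (52 in total) would have about 94% power and there would be no shortfall. The wording per group speaks against that reading. The doubt about 38 is a separate matter, and 87 corrects the attrition step only, without validating 38.

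*The error does not bias the estimate.* True. It concerns the stated justification for the size, not the validity of the intention-to-treat analysis.

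**Conclusion.** The attrition allowance is wrong as written. The article multiplies by 1.559 where it should divide by 0.441, so 59 per group covers a loss of at most 35.6% and not the 55.9% named. At 55.9% loss of the posttest, 26 per group per country remain, or 52 pooled. That figure assumes that non-completers give no posttest, that both groups lose at the same rate and, for the 26, that the requirement applies per country.

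The power cost of this step alone is from 85% to about 69% on the paired or one-sample basis that reproduces 38. On the two-sample basis it is from 58% to 42%, with 71% at 52 pooled.

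A reader might infer that this slip takes the trial from 85% power to 42%. The article does not support that. On the two-sample basis, about 27 of the 43 points are missing before any attrition, because 38 per group does not give 85% power for that comparison. Nor does it follow that the trial will end with 26 per group, since the analysis plan does not restrict the posttest to completers.

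**What to change.** No additional enrolment is needed. Two changes of wording in Research Subjects, with a matching sentence in Data Analyses:

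1. Replace the claim that 59 allows for 55.9% attrition with the statement that 59 per group covers up to 35.6% loss. Give the remaining number and the power at 55.9% loss, both per country (26) and pooled (52). Name the test behind 38, and say whether 38 applies to each country or to the pooled trial.

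2. Stop using programme non-completion as the rate of outcome loss. State that the GAD-7 and the FGI-Checklist are sought at 4 months from every randomised participant in both groups, whatever their attendance. This agrees with the intention-to-treat analysis already planned and makes explicit what the article leaves unsaid.

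The cost is a less favourable stated power and some follow-up reminders for two self-completed questionnaires.

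### The 38 per group for 85% power at d = 0.5 cannot be reproduced from its stated inputs for the between-arm comparison, and its printed alpha of 0.5 contradicts the .05 used for testing

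*Protocol article*

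**What the plan says.** Research Subjects reports a G*Power result: "the required sample size is 38 participants per group (85% statistical power; medium effect size Cohen" d = 0.5), with "a priori probability level of 0.5", and describes it as being "for a linear mixed model (LMM) analysis". After an allowance for attrition, the same section concludes that "we will recruit 59 participants per group in each country", so the 38 is used as a per-country, per-arm requirement.

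Research Design describes "A prospective, parallel randomized controlled trial design involving pre- and posttesting of a treatment group and a control group". Data Analyses names the model terms: "the treatment group, time, and interactions between the treatment group and time will be considered fixed factors". No country term is listed. The significance rule there is that P "values of .05 or less will be considered statistically significant".

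The article does not say whether d is a between-arm, within-person or change-score effect. It also does not give the sidedness of the test, a pre-post correlation, or whether the 85% refers to each country or to both together.

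**The concern.** The sample-size statement gives n, power, effect size and alpha together, so it can be checked. Two things fail. The alpha differs tenfold from the testing level in Data Analyses. The n also does not follow from the other inputs for the contrast the trial exists to make, treatment against usual care through the group-by-time interaction.

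The 85% tells readers how to interpret a result that is not significant. If the real power for a 0.5 SD difference between arms within a country is nearer 58% at the stated 38 per group, a null country-level result would be read as evidence against the intervention when it may only reflect too few participants.

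**Working it through.** **Inputs.** From the article: d = 0.5, power 85%, n = 38 per group, alpha 0.5 (Research Subjects) or .05 (Data Analyses), two equal arms, 59 recruited per arm per country, 55.9% attrition. Assumed because not stated: two-sided testing (one-sided also tried) and the pre-post correlation r (varied). Power is from the noncentral t distribution with 2n − 2 degrees of freedom and noncentrality d·√(n/2).

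**1. Reproducing 38 as a two-arm size.** The normal approximation is n = 2(z₁₋α/₂ + z₁₋β)²/d². At two-sided .05 this is 2(1.960 + 1.036)²/0.25 = 71.8, so 72, or 73 with the t distribution.

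| Alpha | Sides | n per group for 85% (t) | Power at 38 per group |
|---|---|---|---|
| 0.5 (as printed) | two | 23 | 94% |
| 0.5 (as printed) | one | 9 | 99% |
| .05 | two | 73 | 58% |
| .05 | one | 59 | 70% |

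No row gives 38. At two-sided .05, 38 per group has 85% power for d of about 0.70.

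**2. Calculations that do give 38, both at two-sided .05.**
- A paired (within-person) t test with d = 0.5: noncentrality 0.5·√38 = 3.08, power 85.1%, n = 38.
- The total N of a repeated-measures group-by-time interaction with 2 groups, 2 times, f = 0.25 and r = 0.5: λ = N·f²·2/(1 − r) = 38 × 0.0625 × 2/0.5 = 9.5, power 85.1%. In this layout f is one quarter of the between-arm difference in change, so f = 0.25 means 1.0 SD. A 0.5 SD difference (f = 0.125) needs a total of 146, that is 73 per group.

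Neither is a per-group size for a 0.5 SD difference between arms.

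**3. Baseline information at 38 per group, two-sided .05.** Baseline adjustment replaces d by d/√(1 − r²). A change score replaces it by d/√(2(1 − r)).

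| r | Baseline-adjusted | Change score |
|---|---|---|
| 0.3 | 62% | 44% |
| 0.5 | 70% | 58% |
| 0.6 | 77% | 67% |
| 0.70 | 85% | 79% |
| 0.75 | 90% | 86% |

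**4. Pooling the countries.** 2 × 38 = 76 per arm gives 86% with no baseline gain.

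**5. Power at the recruited size, d = 0.5, two-sided .05.** The article's allowance is 38 × 1.559 = 59.2, so 59. If all 55.9% yield no outcome data, 59 × 0.441 = 26 remain per arm per country, or 52 pooled.

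| Comparison | n per arm | No baseline gain | Baseline-adjusted, assumed r = 0.5 |
|---|---|---|---|
| Per country, no loss | 59 | 77% | 87% |
| Per country, worst case | 26 | 42% | 53% |
| Pooled, no loss | 118 | 97% | 99% |
| Pooled, worst case | 52 | 71% | 83% |

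**The case against.** The strongest reply is that the two-sample t test is not the planned analysis. The article names a linear mixed model on pre- and posttest data and never says that d is a between-arm effect. A condensed article may omit a correlation that was entered in G*Power. With a correlation of about 0.70 (baseline-adjusted) or 0.75 (change score), 38 per group does give 85%. The model lists no country term, and pooling 76 per arm gives 86%. This part stands: a reader might infer that 85% is simply false or that the trial as a whole is underpowered, and the document does not establish either. It does not rescue the statement as printed, because no correlation is given and the 38 is turned directly into a per-country recruitment target.

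A reader might also infer that the alpha of 0.5 explains the shortfall. It does not: at 0.5, power with 38 per group would be about 94%, and both calculations that return 38 use .05. A misprint is the likely explanation.

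A third tempting inference is that a paired test or a total N was mistaken for a per-group size. The exact match suggests this, but two different calculations fit and the article identifies neither.

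Finally, the 55.9% is the complement of the 44.1% who completed a web-based programme in the cited study. The article calls it attrition, but not completing a programme is not the same as having no outcome data, and the mixed model keeps participants with incomplete data. The 42% and 71% are therefore a worst case, not an expectation.

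**Conclusion.** The point holds as a failure of reproduction. The stated inputs do not yield 38 per group for the planned between-arm comparison, and the printed alpha contradicts the testing level. At two-sided .05 with no baseline gain, 73 per group are needed and 38 gives about 58%. Reaching 85% at 38 per group needs a correlation of about 0.70 to 0.75 that the article does not state, or a pooled comparison that its per-country use of 38 does not describe.

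These figures assume d = 0.5 is a between-arm difference in outcome SD units, equal allocation and a two-sided test. The recruited total of 236 is not shown to be inadequate. Depending on pooling, baseline gain and losses, power at that size runs from 42% to 99% over the cases tabulated.

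**What to change.** In Research Subjects, correct alpha to 0.05 and state that it is two-sided. Keep the 236 participants. Replace the claim of 38 per group for 85% power with the between-arm power at d = 0.5 for the recruited numbers, and state:
- that d is the between-arm difference, and in which SD units;
- the assumed pre-post correlation and whether the calculation is baseline-adjusted or on change scores;
- whether the powered comparison is per country or pooled, which is the investigators' choice;
- power without loss and in the worst case where every assumed non-completer also lacks outcome data.

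With no baseline gain, the figures to print are 77% per country and 97% pooled, falling to 42% and 71% in the worst case. At an assumed correlation of 0.5 with baseline adjustment they are about 87% and 99%, falling to 53% and 83%.

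The cost is wording only, with no change to recruitment. The per-country power may look less favourable than the 85% now printed.
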